### Study participants and recruitment

In this clinical trial, 106 patients scheduled to undergo elective surgeries in prone position will be recruited from February 1, 2022 to February 1, 2023. Participants will receive written information about the study and provide written informed consent. We will enroll patients who meet the inclusion criteria and sign informed consent one day before surgery.

### Inclusion criteria

Patients who plan to undergo elective surgery in prone positions will be included according to the criteria below: (1) ASA physical status II and III; (2) ≥ 65 years old; (3) baseline mini-mental state examination (MMSE) [15] score > 23 points evaluated one day before surgery.

### Exclusion criteria

Patients who meet the following criteria will be excluded: (1) hypoalbuminemia or hypoxemia; (2) anemia; (3) chronic lung disease; (4) mental illness; (5) BMI ≥ 35 kg/m^2^; (6) contraindications to PEEP [16] (right heart failure, high intracranial pressure, or hypovolemic shock).

### Discharge criteria

The discharge criteria are as follows: (1) baseline rSO2 < 60%; (2) the operation time > 4 h, (3) intraoperative blood loss > 800 ml; (4) interruption of study protocol.

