### Randomization and blinding

The trial is single-blind because the attending anesthesiologist will collect data and perform PEEP titration without being blinded to the group assignments. Based on a computer-generated randomization sequence performed by an independent investigator, the selected participants will be randomized into Group I and Group C. Envelopes with random numbers will be opened when patients enter the operating room. The allocation ratio is 1:1. Postoperative information collection and the following data analyses will be performed by another researcher who will not participate in this study and know about the grouping allocation.

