### Interventions

Noninvasive blood pressure (NIBP), electrocardiogram, pulse oxygen saturation, bispectral index (BIS), body temperature, and rSO_2_ of patients in each group will be routinely monitored after entering the operating room. We will place two brain oxygen electrodes 4 cm from the forehead to the brow arch (one on the left and another on the right) to measure rSO_2_ by using near-infrared spectroscopy (NIRS). After placement of monitors, radial artery puncture and catheterization will be performed under local anesthesia, allowing intermittent blood gas analyses and continuous hemodynamic monitoring.

Patients will receive intravenous propofol (2 mg/kg), sufentanil (0.3 µg/kg), and cisatracurium (0.15 mg/kg) for anesthesia induction and tracheal intubation after preoxygenated (inspired oxygen fraction of 0.8) for three minutes. During surgery, sevoflurane inhalation and continuous intravenous remifentanil and propofol infusion will be employed to maintain BIS between 40 and 60. Intermittent administration of cis-atracurium will provide sufficient muscle relaxation. Vasoactive drugs will be used to maintain mean arterial pressure (MAP) and heart rate within ± 20% of the baseline. The core temperature will be maintained above 36.0 ℃ by using a forced air warming system. Subsequently, when patients can respond to verbal commands, they will undergo extubating procedures and be transferred to the postanesthesia care unit (PACU) until fully awake. Patients will routinely receive intravenous patient-controlled analgesia (PCIA) to control postoperative pain.

Mechanical ventilation will be maintained with V_T_ 6 ml/kg PBW, FIO_2_ of 50%, and I: E of 1:2 with PCV-VG mode. After the prone position is established, both groups will receive the recruitment maneuver by squeezing a reservoir bag up to 30–40 cm H_2_O for 15–20 s. The initial respiratory rate will be set to 12 breaths per minute and P_ET_CO_2_ is maintained in the range of 40 ± 5 mm Hg by adjusting the respiration rate.

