The patients in both groups will receive the PEEP of 5 cm H_2_O after endotracheal intubation, and this PEEP level will be maintained throughout the whole procedure in the group C. After the prone position is set up, patients in Group I will receive optimal individualized PEEP identified by an incremental PEEP titration protocol (Fig. 2). The PEEP titration method is as follows: each PEEP level (4, 6, 8, 10, 12, 14, 16 cm H_2_O) will be maintained for 60 s. Meanwhile, we will record the Cdyn at each PEEP level. We will select the optimal PEEP level based on the maximum Cdyn and maintain it throughout the whole study period. If circulatory instability occurs during PEEP titration, intravenous infusion of noradrenaline will be used to maintain MAP ≥ 55mmHg.

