### Outcome assessment

The primary endpoint of this trial will be the incidence of POD within 3 days after surgery. POD will be determined by an independent researcher who will not know the group assignment using CAM [17]. The investigator will participate in a training session including symptoms and diagnosis of delirium and will not know the group assignment. The researcher will assess POD once daily, between 6: 00 am to 8: 00 am. Four key delirium characteristics consist of CAM diagnostic criteria: (1) acute onset and disease fluctuations, (2) inattention, (3) changes in consciousness, and (4) disordered thinking. Delirium will be defined as the presence of (1) and (2), accompanied by (3) or (4) or both [7].

The secondary outcomes will include perioperative rSO_2_ measurement, arterial blood gases, respiratory variables, and plasma concentrations of interleukin (IL)-1β, IL-6, and NSE. The baseline rSO_2_ will be obtained within 2 minutes before anesthesia induction and averaged. Additionally, intraoperative rSO_2_ values will be continuously measured and recorded using a cerebral oximeter at the following timepoint: T_0_: after entering the operating room; T_1_: 5 minutes after starting mechanical ventilation in the supine position; T_2_: 60 minutes after turning over; and T_3_: 5 minutes after taking in the supine position. The serum concentrations of interleukin (IL)-1β, IL-6, and NSE will be determined by ELISA kits. We will collect the blood samples 15 minutes before anesthesia induction (T_0_) and postoperative day 1.

Arterial blood gases will be measured at T_1_ to T_4_ (after breathing air in PACU for 20 minutes). Respiratory variables including P_ET_CO_2_, PEEP, P_peak_, mean airway pressure (P_mean_), Cdyn, PaO_2_/FiO_2_, A-aDO_2_, V_D_/V_T,_ and Qs/Qt will be recorded at T_1_ to T_3_. Each patient will receive two ultrasound examinations at T_1_ and T_4_. And lung ultrasound scans will be performed by an experienced anesthetist who will not know the group allocations. As described previously [18, 19], each hemithorax will be alienated into 6 quadrants and each region will be assigned a score of 0 to 3 according to the different signs of B-line, subpleural consolidation and pleural line under ultrasound scan. The LUS will be calculated to quantitatively assess the aeration loss by adding all scores up.

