### Sample size calculation

G∗power (version 3.1.9.6) is used to calculate the sample size. A total of 16 (8 in the I group and 8 in the C group) patients were included in our preliminary experiments. The number of patients diagnosed with POD was 2 in the I group and 3 in the C group, respectively. On this basis, the calculated sample size that would provide 80% power to detect this difference at a two-sided significance level of 0.05 was 42 patients per group. Considering a dropout rate of 20%, 106 patients will be enrolled in this study.

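### The discharge criteria apply after allocation, and three of the four can arise once the arms differ, so removing these patients can make the groups compared for delirium differ from those randomised

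*Protocol article*

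**What the plan says.** The Discharge criteria section of the protocol article, separate from the inclusion and exclusion criteria, lists "baseline rSO2 < 60%; (2) the operation time > 4 h, (3) intraoperative blood loss > 800 ml; (4) interruption of study protocol". It does not define discharge or interruption.

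The order of events comes from other sections:

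- Randomization and blinding: "Envelopes with random numbers will be opened when patients enter the operating room". In addition, "the attending anesthesiologist will collect data and perform PEEP titration without being blinded to the group assignments".
- Interventions: rSO2 and the other signals "will be routinely monitored after entering the operating room". Both groups have the same PEEP after intubation, and then "After the prone position is set up, patients in Group I will receive optimal individualized PEEP identified by an incremental PEEP titration protocol".
- Outcome assessment: "The baseline rSO_2_ will be obtained within 2 minutes before anesthesia induction and averaged". The endpoint is short: "The primary endpoint of this trial will be the incidence of POD within 3 days after surgery".
- Sample size calculation: "Considering a dropout rate of 20%, 106 patients will be enrolled in this study".

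No section says whether a discharged patient is still assessed with CAM or still counted in the delirium comparison. Statistical methods names tests only.

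**The concern.** Randomisation makes the arms comparable at the moment of allocation. A rule that removes patients afterwards keeps that comparability only if removal is unrelated to the arm, or unrelated to the outcome. Here three of the four criteria can be met after ventilation has begun to differ, while the person collecting data in the operating room knows the group. If more patients leave one arm than the other, or different kinds of patients leave, and their delirium risk differs from that of the rest, the primary comparison shows a difference that the treatment did not cause. Even balanced removal discards endpoint events from a small trial. CAM assessments that were never made cannot be recovered by a later analysis plan.

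**Working it through.** **Step 1: when each criterion becomes known.** The sequence from the sections cited is: entry and envelope; rSO2 monitoring and baseline reading; induction; prone position; arms diverge; surgery.

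| Criterion | After the envelope is opened? | Can arise after the arms diverge? |
|---|---|---|
| Baseline rSO2 < 60% | Yes | No (read before induction) |
| Operation > 4 h | Yes | Yes |
| Blood loss > 800 ml | Yes | Yes |
| Protocol interruption | Yes | Yes; titration exists only in Group I |

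**Step 2: the plan's own allowance.** 42/(1 − 0.20) = 52.5, rounded up to 53 per arm, and 2 × 53 = 106. This step reproduces. The margin is 106 − 84 = 22 patients. (The 42 itself does not reproduce: the pilot rates of 3/8 and 2/8 need about 215 per group. That is a separate problem, and nothing here depends on it.)

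**Step 3: what removal could do when there is no treatment effect.** Let p be the delirium risk in all randomised patients of an arm, f the fraction removed and r the risk in those removed. The risk among those left is

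(p − f × r)/(1 − f).

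From the documents: p = 5/16 = 31.25%, the pooled pilot rate, used for both arms, and 53 per arm. Assumed, with no source in the documents: f and r.

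- 20% removed in each arm, r = 50% in both: (0.3125 − 0.100)/0.80 = 26.6% in each. Difference 0.
- 25% in I and 15% in C, r = 50%: (0.3125 − 0.125)/0.75 = 25.0% against (0.3125 − 0.075)/0.85 = 27.9%. Difference −2.9 points.
- The same removal, r = 60%: (0.3125 − 0.150)/0.75 = 21.7% against (0.3125 − 0.090)/0.85 = 26.2%. Difference −4.5 points.
- Reversed, 15% in I and 25% in C: +2.9 and +4.5 points.
- A harsher assumption, 30% in I and 10% in C: −6.0 points (r = 50%) and −9.1 points (r = 60%).
- Any removal pattern with r = 31.25%: difference 0.

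By normal approximation, the two-sided type I error is about 6% and 8% for the 25%/15% cases, and about 9.5% and 17% for the 30%/10% cases.

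Equal fractions alone are not enough. With 20% removed from each arm but r = 60% in I and 50% in C, the remaining risks are (0.3125 − 0.120)/0.80 = 24.1% and 26.6%, a difference of −2.5 points.

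**The case against.** The strongest case on the other side has four parts.

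- **The article does not say that discharged patients lose CAM or leave the analysis.** Analysis sets are commonly left to a full protocol or SAP. This stands in part: loss from the comparison is an inference. But leaving hospital cannot be what is meant by an rSO2 threshold or a long operation, so removal from the study is the only sensible reading. The rule itself is stated here, not left to another document.
- **The criteria are not alike.** This stands. Baseline rSO2 is a reading against a fixed threshold, taken while both groups are treated identically. Treatment cannot change it.
- **Dependence on arm is thinly documented.** This also stands in part. No section links PEEP to blood loss or to operation time, and individualised PEEP need not be higher than control, since titration starts at 4 cm H2O against the control's 5. Circulatory instability during titration is to be treated, and Statistical methods stratifies on MAP < 55 mmHg during titration, so those patients appear meant to stay in the analysis. There remains an undefined interruption criterion beside a procedure that only one arm undergoes, with the allocation known to the person performing it.
- **The bias figures are assumed.** They are. On the milder assumptions the false difference is less than half of its standard error (about 9 to 10 points), so the effect on type I error is modest.

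**Conclusion.** The concern holds in a limited form. The timing is certain from the text: all four criteria act on allocated patients, and three can arise after the arms diverge. If those patients are dropped, the analysed groups can differ from the randomised groups, most seriously through protocol interruption. Baseline rSO2 mainly costs patients, and is a source of bias only if applied unevenly by someone who knows the group.

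Size and direction cannot be derived from the documents. The 3 to 4.5 points rest on no treatment effect, a 31.25% risk in both arms, removal of 25% against 15%, and a 50–60% risk in those removed. The sign follows whichever arm loses more.

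A reader might go further in three ways that the documents do not support:

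- **That the bias favours Group I.** Nothing shows which arm would lose more patients.
- **That the 20% allowance means 22 such removals are expected.** It is a planning figure, not tied to these criteria, and neither a count nor a ceiling of them.
- **That those removed are the patients most prone to delirium.** The article links delirium to low cerebral saturation only, which is the one criterion that treatment cannot affect. It gives no delirium risk for long surgery or blood loss.

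**What to change.** 1. Read baseline rSO2 before the envelope is opened, and make a value below 60% a pre-randomisation exclusion.
2. State that operation time, blood loss and protocol interruption do not end delirium follow-up. Continue CAM to day 3 and include all randomised patients, by allocated group, in the primary analysis.
3. Use the set without these patients only as a sensitivity analysis.

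The cost is small. A blinded assessor already performs CAM daily, and Safety evaluation already has researchers visiting every patient daily until hospital discharge. What is added is a slightly later moment for opening the envelope, a few more CAM visits, an amendment, and slight dilution from patients whose intervention was incomplete. In return, up to 53 per arm could be analysed. Delaying the envelope further, until the patient is prone, is optional and does not address the other three criteria.

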### Interventions

Noninvasive blood pressure (NIBP), electrocardiogram, pulse oxygen saturation, bispectral index (BIS), body temperature, and rSO_2_ of patients in each group will be routinely monitored after entering the operating room. We will place two brain oxygen electrodes 4 cm from the forehead to the brow arch (one on the left and another on the right) to measure rSO_2_ by using near-infrared spectroscopy (NIRS). After placement of monitors, radial artery puncture and catheterization will be performed under local anesthesia, allowing intermittent blood gas analyses and continuous hemodynamic monitoring.

Patients will receive intravenous propofol (2 mg/kg), sufentanil (0.3 µg/kg), and cisatracurium (0.15 mg/kg) for anesthesia induction and tracheal intubation after preoxygenated (inspired oxygen fraction of 0.8) for three minutes. During surgery, sevoflurane inhalation and continuous intravenous remifentanil and propofol infusion will be employed to maintain BIS between 40 and 60. Intermittent administration of cis-atracurium will provide sufficient muscle relaxation. Vasoactive drugs will be used to maintain mean arterial pressure (MAP) and heart rate within ± 20% of the baseline. The core temperature will be maintained above 36.0 ℃ by using a forced air warming system. Subsequently, when patients can respond to verbal commands, they will undergo extubating procedures and be transferred to the postanesthesia care unit (PACU) until fully awake. Patients will routinely receive intravenous patient-controlled analgesia (PCIA) to control postoperative pain.

Mechanical ventilation will be maintained with V_T_ 6 ml/kg PBW, FIO_2_ of 50%, and I: E of 1:2 with PCV-VG mode. After the prone position is established, both groups will receive the recruitment maneuver by squeezing a reservoir bag up to 30–40 cm H_2_O for 15–20 s. The initial respiratory rate will be set to 12 breaths per minute and P_ET_CO_2_ is maintained in the range of 40 ± 5 mm Hg by adjusting the respiration rate.

The patients in both groups will receive the PEEP of 5 cm H_2_O after endotracheal intubation, and this PEEP level will be maintained throughout the whole procedure in the group C. After the prone position is set up, patients in Group I will receive optimal individualized PEEP identified by an incremental PEEP titration protocol (Fig. 2). The PEEP titration method is as follows: each PEEP level (4, 6, 8, 10, 12, 14, 16 cm H_2_O) will be maintained for 60 s. Meanwhile, we will record the Cdyn at each PEEP level. We will select the optimal PEEP level based on the maximum Cdyn and maintain it throughout the whole study period. If circulatory instability occurs during PEEP titration, intravenous infusion of noradrenaline will be used to maintain MAP ≥ 55mmHg.

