Postoperative VAS scores will be checked by the ward doctors who will not be involved in this study. When the VAS score is>3 points, participants will receive intravenous Flubiprofen infusion with the dose of 50 mg. The analgesic drug consumption will also be recorded.

Parameters calculating will use formulas below:

$${\mathrm V}_{\mathrm D}/{\mathrm V}_{\mathrm T}=\;(\mathrm{PaCO}2-\;{\mathrm P}_{\mathrm{ET}}{\mathrm{CO}}_2)/{\mathrm{PaCO}}_2$$

$$\mathrm{Qs}/\mathrm{Qt}\;=\;(\mathrm{PA}-{\mathrm{aDO}}_2\times0.0031)\;\div\;(\mathrm{PA}-{\mathrm{DO}}_2\times\;0.0031\;+\;5)$$

$$\mathrm{PA}-\mathrm{aDO}2=\;\lbrack{\mathrm{FiO}}_2\times\;({\mathrm P}_{\mathrm B}-\;{\mathrm P}_{\mathrm H2\mathrm O})\rbrack\;-\;{\mathrm{PaCO}}_2/\mathrm R\;-\;\mathrm{PaO}2\;$$

$$(\mathrm{PB}=\;760\mathrm{mmHg},\;{\mathrm P}_{\mathrm H2\mathrm O}=\;47\mathrm{mmHg},\;\mathrm R\;=\;0.8)$$

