### Safety evaluation

The researchers will monitor all adverse events (AEs) associated with the PEEP titration procedure. AEs are defined as hypotension, significant cardiac arrhythmias, pneumothorax, significant disability or incapacity, and even death. The researchers will visit all patients in the trial daily until they are discharged from the hospital and record the occurrence of all AEs in detail. Once AEs occur, the trial will be suspended and an investigation will begin.

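### Adverse events are tied to the PEEP titration that only Group I undergoes, and vasoactive drug use is not a stated outcome, so the arms cannot be compared like for like on haemodynamic harm

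*Protocol article*

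**What the plan says.** All references are to the protocol article.

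- **Assigned PEEP (Interventions).** Both arms start at 5 cm H2O. For the control arm, "this PEEP level will be maintained throughout the whole procedure in the group C". Group I is titrated once prone, through levels of 4 to 16 cm H2O. Then: "We will select the optimal PEEP level based on the maximum Cdyn and maintain it throughout the whole study period".
- **Blood pressure support (Interventions).** During surgery, with no restriction by arm: "Vasoactive drugs will be used to maintain mean arterial pressure (MAP) and heart rate within ± 20% of the baseline". For the titration step, and so for Group I only: "If circulatory instability occurs during PEEP titration, intravenous infusion of noradrenaline will be used to maintain MAP ≥ 55mmHg".
- **Monitoring (Interventions).** Every patient has a radial arterial line, "allowing intermittent blood gas analyses and continuous hemodynamic monitoring".
- **Safety (Safety evaluation).** "The researchers will monitor all adverse events (AEs) associated with the PEEP titration procedure". Hypotension and significant arrhythmia are both listed as adverse events, and hypotension is given no threshold. The same section has all patients visited daily until discharge, with all adverse events recorded in detail.
- **Outcomes (Outcome assessment).** "The secondary outcomes will include perioperative rSO_2_ measurement, arterial blood gases, respiratory variables", followed by the plasma markers. Lung ultrasound and pain scores are also collected. The one drug whose use is said to be captured is the analgesic: "The analgesic drug consumption will also be recorded".
- **Analysis (Statistical methods).** The only haemodynamic variable is whether MAP falls below 55 mmHg during titration. It is used as a stratification factor for the delirium comparison, not as a safety outcome.

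**The concern.** A higher PEEP kept for the rest of the operation may have a haemodynamic cost. When pressure is held near baseline with drugs, that cost may appear less as hypotension than as the amount of drug needed to prevent or correct it. A fair account of it needs two things: the same event definition and time window in both arms, and a record of the support given.

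The article states neither. Its safety rule attaches events to a procedure that one arm does not have. Its outcomes and analysis leave out vasoactive use, and MAP after titration. If Group I needs more support, the trial could report similar pressures in the two arms and a set of adverse events with no defined control counterpart.

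Interpretation is also at stake. The Discussion links reduced cardiac output and brain perfusion pressure to low rSO2, and low rSO2 to delirium. Vasoactive treatment that differs by arm would be useful to know when reading the rSO2 and delirium results.

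**Working it through.** The article gives no figure to reproduce on this point. The check is to set the exposure beside what is recorded about it.

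**1. Exposure.** The PEEP difference between arms after titration is the selected level minus 5 cm H2O.
- Lowest: 4 − 5 = −1 cm H2O.
- Highest: 16 − 5 = +11 cm H2O.

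The selected level is held for the rest of the procedure. Under Discharge criteria, patients whose operation exceeds 4 h leave the study, so 4 h is the longest operation retained.

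**2. What is stated as recorded.**

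| Item | Group I | Group C |
|---|---|---|
| Adverse events associated with titration | Yes | No titration, so nothing to attribute to it |
| MAP below 55 mmHg during titration | Yes | No titration |
| MAP or hypotension over the period at assigned PEEP, as an outcome | Not stated | Not stated |
| Vasoactive drug use or dose | Not stated | Not stated |
| Analgesic consumption | Yes | Yes |

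The two items closest to haemodynamic harm are both defined through titration. The later sentence about visiting all patients and recording all events points to wider capture, but the section does not say which rule governs intraoperative events in Group C. A daily visit is also a poor way to find out how much vasoactive drug was given in theatre.

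**3. Can the planned stratified test fill the gap?** In a stratum with n_I patients in Group I and n_C in Group C (N in total), with a and c delirium cases respectively, the Mantel–Haenszel risk ratio adds a·n_C/N to the numerator and c·n_I/N to the denominator. Group C has no titration, so the stratum with MAP below 55 mmHg during titration has n_C = 0 and therefore c = 0. Both terms are zero and the stratum contributes nothing. The test gives no between-arm haemodynamic comparison.

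**4. The two MAP limits.** The general rule has a lower limit of 0.8 × baseline MAP. The titration rule has a floor of 55 mmHg. They coincide when 0.8 × baseline = 55, that is, baseline = 55/0.8 = 68.75 mmHg. For any higher baseline, a MAP between 55 mmHg and 0.8 × baseline satisfies the titration rule but lies outside the general range. The article does not say whether the titration rule replaces the general one for that step. With no threshold for the hypotension event, it is unclear which limit would define one.

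**The case against.** **This is an article, and Table 1 is not shown.** Vasoactive drugs may well be logged on the anaesthesia record or case report form, and an article need not list every field. That stands as far as the omission goes, and the point should not be read as saying that the data will not exist. It does not remove the stated safety scope, which is tied to a procedure in one arm. The article also found room to say that analgesic use is recorded.

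**Treated hypotension can still be counted.** A reader might infer that drug support removes the harm before it can be recorded. The documents do not support that. Nothing excludes a treated episode from being an adverse event, the arterial line would show the fall that prompted treatment, and all events are to be recorded in detail. Arrhythmia is a listed event too. Under-counting is possible but not certain.

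**The wording concerns attribution, not a time window.** A reader might infer that events are monitored only during the seven 60-second titration steps, a small fraction of a 4 h operation. That does not follow. The text speaks of events associated with titration, lists disability and death, and follows patients to discharge. The fault is that attribution to titration has no counterpart in Group C.

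**Direction of bias.** A reader might infer that the safety comparison is pushed toward no difference. This is not established. Drug support could mask a Group I excess, but counting events linked to titration could produce more events in Group I. No between-arm safety test is specified either.

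**Effect on the primary endpoint.** Vasoactive need caused by the assigned PEEP is part of that strategy's effect, and leaving it unrecorded does not bias the randomised delirium comparison. The Discussion passage on cardiac output concerns the turn to prone, which happens in both arms. These objections stand. The loss is in safety reporting and explanation.

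**Conclusion.** The point holds in a limited form. As written, the safety rule attaches adverse events to a procedure that only Group I undergoes, while the exposure of interest is the PEEP maintained afterwards. Pressure is supported with drugs in both arms, the stated outcomes and analyses omit that support, and hypotension has no threshold. Hypotension events alone may therefore under-count a haemodynamic difference, and the stated safety data do not allow a like-for-like comparison.

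No numerical size can be attached, because the article gives no rate of vasoactive use or hypotension in either arm. The exposure left without a stated haemodynamic comparison is a PEEP difference of −1 to +11 cm H2O, in operations of up to 4 h. The conclusion assumes that Table 1 and the full protocol do not already define events for both arms or list vasoactive use. If they do, only the wording of the safety section and the two MAP limits need attention.

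**What to change.** 1. **Safety evaluation.** Reword the scope so that adverse events are recorded in both arms, with the same definitions, over the whole period at the assigned PEEP. Use the same start and stop in each arm, for example from prone positioning to extubation. Events during titration can be flagged as a subset. State the definition of hypotension to be used for recording.
2. **Outcome assessment.** Add a descriptive safety outcome, reported by arm: vasoactive drug use (yes/no), total dose for each agent, and MAP excursions outside the protocol's own range. No hypothesis test is needed.
3. **Interventions.** The authors should reconcile the general MAP range with the separate limit during titration, and say which applies when. This review takes no view on what the limit should be. The excursion measure in item 2 depends on the answer.

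**Cost.** One more form page and one more safety table. The arterial line and the anaesthesia record should supply the data, so no extra patient or procedure is needed. The article reports 12 participants already recruited; their values could be taken from existing records where these are complete.
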